The questionnaire was used as a screening instrument and also served as a baseline measurement for the participants of the trial. Among the respondents (n = 3,689, see figure 1), we found 872 persons who reported their health status as poor (on a scale ranging from 1–10 points, report marks 1–5 are considered poor, 6–7 fairly good, and 8–10 good). Our previous home visitation study indicated positive effects for this subgroup. Five persons did not sign the informed consent form and 273 persons with a poor health status did not want to participate in the study. Of the remaining 594 persons, we excluded those who already received home nursing care at baseline, in order to avoid contamination of (other) nursing care. Referral to nursing services after the start of the intervention period has no consequences for the scheduled home visits in the intervention group. It is regarded as a possible effect of the intervention and it is registered as outcome in terms of service use. Persons on a waiting list for admission to nursing homes or homes for the elderly were also excluded. The local independent committee dealing with applications for the use of care services already granted them this service. It is likely that most of them already receive regular supervision of professional caregivers. Six persons were excluded on the advice of their GPs. They were severely or terminally ill and would probably die within 6 months. On the basis of these exclusion criteria, a total of 102 persons were excluded.

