#### Randomisation

The baseline measurements included questions on relevant prognostic factors related to the health status and service use. Before randomisation we divided the 330 participants into two groups: couples (n = 46) and those for whom this did not apply (n = 284). In this way we made sure that eligible persons who lived together, were always allocated to the same study group (in order to avoid contamination of the intervention). The 23 couples were divided into 3 strata on the basis of their (added) score on functional status (0–4, 5–7 or more than 7 out of 18 activities that cannot be carried out independently). The other 284 participants were stratified into 8 strata based on 3 prognostic factors – two health-variables and one service use-variable:

1. functional status (0–2 or more than 2 activities that the elderly cannot carry out independently)

2. changes in health during the 3 months prior to completion of the questionnaire (same/better or worse)

3. contact with a medical specialist in the 3 months prior to completion of the questionnaire (contact yes or no).

The participants in each of the 8 strata were then randomised into either a control or intervention group using a computer generated randomisation list with a block length of 4 [15]. Randomly, we allocated 160 persons to the intervention group and 170 persons to the control group. Table 2 shows the baseline characteristics of the intervention and control group. The study groups are well matched; there were hardly any differences between the groups at the start of the study.

The participants in the intervention group were assigned to one of the three home nurses. This depended on the location of their GP practice, as each nurse was assigned to a number of GP practices. We assumed that this would facilitate the co-operation with the GPs. Each nurse was responsible for 52–56 elderly during the intervention period.

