### Statistical analyses

The main analyses will be conducted according to the intention-to-treat principle. Analysis of primary and secondary endpoints will be performed using relevant significance tests (e.g., chi-square, t-test or analysis of variance). Regression techniques will be used, if necessary, to estimate the effects for the various outcome measures, adjusting for small differences between the groups at the start of the study. In addition, we will conduct per-protocol analyses; these are restricted to those participants who complied fully with the intervention protocol and outcome measurements. Preplanned subgroup analysis will be performed for the following subgroups: living alone/together; health deterioration over the previous 3 months; functional status and locus of control. Differences in approaches between the nurses will be investigated.

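### Covariate adjustment is made to depend on observed baseline differences, so the prognostic factors used in the randomisation would tend to drop out of the analysis, at a cost in precision

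*Protocol article*

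**What the plan says.** Under Statistical analyses, primary and secondary endpoints are to be "performed using relevant significance tests (e.g., chi-square, t-test or analysis of variance"). Covariates enter through one further sentence, which concerns differences seen at baseline: "Regression techniques will be used, if necessary, to estimate the effects for the various outcome measures, adjusting for small differences between the groups". The section gives no criterion for when this is necessary, names no covariates, and does not commit to the stratification factors or the baseline score.

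Three other statements bear on this:

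- Randomisation, on those not in couples: "The other 284 participants were stratified into 8 strata based on 3 prognostic factors". The factors are functional status, recent change in health and recent contact with a specialist.
- Randomisation, on couples: "The 23 couples were divided into 3 strata on the basis of their (added) score on functional status". On the result it reports: "The study groups are well matched; there were hardly any differences between the groups at the start of the study".
- Identification of eligible participants: "The questionnaire was used as a screening instrument and also served as a baseline measurement for the participants of the trial".

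**The concern.** Stratification makes the arms alike on the chosen factors by design. A rule that adjusts only when the arms differ will therefore seldom adjust for those factors, although they were chosen because they predict outcome. The prognostic information is used in the allocation and then left out of the standard error.

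Two things are at stake:

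- **Precision.** A test that ignores balanced prognostic factors has a standard error that is too large and is conservative. For scale outcomes, leaving out the baseline score also gives up power.
- **Freedom of choice.** Because the condition is undefined, the analyst may hold both an adjusted and an unadjusted result before deciding which to report. The Time plan says the 12-month questionnaires have already been returned at a 95% rate, so the model is best fixed before the arms are compared.

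**Working it through.** **1. The plan's own figure.** The sample size (65% v 45%, one-sided α = 0.05, power 0.90) is an unadjusted calculation:

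n = [1.645·√(2·0.55·0.45) + 1.282·√(0.65·0.35 + 0.45·0.55)]² / 0.20² = 104.1 per group (the plan has 104). 104/0.7 = 148.6 (the plan has 150).

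The figures reproduce. The sample size is not in question.

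**2. Inputs for the rest.** Eight strata and blocks of 4 come from Randomisation. Some runs used 112 v 119 evaluable, which is 160 and 170 less the planned 30% loss (231 in all). The documents give neither the share of outcome variance explained by the strata (R²) nor the baseline–outcome correlation (r). Both are assumed ranges.

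**3. Ignoring the stratification factors.** R² here is only the variance explained by the factors that randomisation balanced. The real size of a nominal two-sided 5% unadjusted test is about 2·[1 − Φ(1.96/√(1 − R²))]. The simulation used 8 strata, blocks of 4, n = 231 and 6,000 runs per setting, with the effect set for 80% power when strata explain nothing.

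| Assumed R² of strata | Size, formula | Size, simulated | Power unadjusted | Power adjusted for strata |
|---|---|---|---|---|
| 5% | 4.4% | 4.2% | 80% | 81% |
| 10% | 3.9% | 4.5% | 81% | 84% |
| 20% | 2.8% | 3.1% | 82% | 88% |
| 30% | 1.9% | 2.0% | 84% | 92% |

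The simulation standard error of a 5% rate is √(0.05·0.95/6000) = 0.3 percentage points, which accounts for the uneven first two rows. A second simulation (n = 280, 8,000 runs) gave 4.6% and 3.9% at R² of 5% and 10%.

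**4. Leaving out the baseline score (continuous outcomes).** Adjustment multiplies the variance by 1 − r². Power for an effect that has 80% unadjusted is Φ(2.802/√(1 − r²) − 1.96).

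| Assumed r | Variance factor | Equivalent sample, 1/(1 − r²) | Power |
|---|---|---|---|
| 0.3 | 0.91 | 1.10 | 84% |
| 0.5 | 0.75 | 1.33 | 90% |
| 0.7 | 0.51 | 1.96 | 97.5% |

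This is a separate argument from step 3. Omitting a baseline score that was not stratified costs power but leaves the size at 5%. In the second simulation, with total R² held at 30%, size was 5.0% when all of it came from an unstratified baseline score, 4.5% when 5 points came from strata, and 1.9% only when all 30 points did.

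**5. What the trigger does to type I error.** Simulated two-sided error at nominal 5%, 112 v 119, 10,000 runs, for r = 0.3 / 0.5 / 0.7:

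- Adjust only if the baseline test gives p < 0.05, simple randomisation: 5.0 / 4.7 / 3.7%.
- Same rule, covariate stratified: 4.4 / 2.9 / 1.9%. The unadjusted test gave the same values, so the trigger makes almost no difference.
- Report the more favourable of the adjusted and unadjusted results, simple randomisation: 6.6 / 7.7 / 8.4%.
- Same choice, covariate stratified: 5.1–5.7%.

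Only the selective choice inflates error, and only slightly when the covariate is itself a stratification factor.

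**The case against.** **The article is condensed, and an analysis plan could name the covariates.** True of a covariate list. But the article does more than stay silent: it states a conditional rule tied to baseline differences. Applied to groups with "there were hardly any differences between the groups at the start of the study", that rule leads mostly to no adjustment. That last step is inference, since hardly any is not none and small differences are a low bar, but it is the natural reading. The list of tests is also open and includes analysis of variance, which could carry the strata as factors; the text does not say that it will.

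**The rule lets the data choose the model and so threatens the validity of a positive result.** A reader might infer this. The documents do not support it. Choosing covariates on baseline imbalance uses no outcome data, and step 5 shows that the trigger does not raise the error rate. Inflation needs selective reporting between two results, which the text permits by leaving the condition undefined but does not plan.

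**The test size could be put as low as 1.9% by counting strata and baseline together.** Also tempting, and wrong. The low sizes apply only to variance explained by the stratified factors, and 30% from three yes/no factors is a strong assumption.

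**Baseline adjustment does not fit every outcome.** This stands. The outcome that sized the trial is better or same versus worse or deceased relative to the start, so it already refers to baseline, and entry was restricted to marks 1–5, which narrows the baseline self-rating. Change in self-reported problems is likewise a change measure, and mortality has no baseline value. For these, the randomisation factors are the relevant covariates.

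**Couples.** Partners were allocated together, and correlation between them makes naive standard errors too small, the opposite direction to step 3. That is a separate matter, and a covariate for couple status does not deal with it.

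**Conclusion.** The point holds in a limited form. The stated rule would tend to leave out the covariates most likely to predict outcome, and what it costs is mainly precision. With strata explaining an assumed 5–10% of variance, the unadjusted test runs at roughly 4–4.6% instead of 5% and gives up about 1 to 3 points of power; the loss grows if they explain more. For continuous scores such as functional status and quality of life, an assumed correlation of 0.3–0.7 means that adjustment would cut the variance by 9–49%. These sizes rest on assumed ranges, because the documents give neither quantity. The analysis is not invalid, and the trigger alone does not inflate type I error. What remains beyond precision is that the undefined condition leaves room to choose between results.

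**What to change.** Replace the conditional sentence with a fixed rule: each primary and secondary effect is estimated by a regression suited to the outcome, adjusted whatever the observed imbalance for

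- the randomisation factors as they were used: functional status, recent health change and specialist contact for those not in couples; couple status and the functional-status stratum for couples;
- the baseline value of the outcome where one exists (functional status and quality of life scores, for example, but not mortality).

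Show the unadjusted test as a sensitivity analysis.

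The cost is wording. The randomisation factors are known for everyone randomised, and the screening questionnaire supplies the baseline values; the Discussion puts missing values at 0–2% for most variables. Correlation between partners needs its own provision, which this change does not supply.

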#### Economic evaluation

A cost-effectiveness analysis will be carried out in which we consider costs from a societal perspective. The economic evaluation will measure and evaluate the 'real' costs. In this study we will include direct health care costs, i.e. costs made for the home visit programme and health care costs made by the participants. Costs of the intervention programme consist of costs for the screening procedure, salaries of the nurses, travel expenses, costs of training sessions for the nurses, etc. Health care costs include costs of inpatient and outpatient treatment, consultation by GPs and other medical practising specialists, physiotherapy, medication, professional home care, nursing home, meals on wheels, aids and appliances, etc. In order to estimate the costs, the quantity of each resource will be multiplied by its assigned unit cost of price.

Direct non health care costs (e.g., the travel costs made by participants) are not included. These should preferably be gathered prospectively by means of a cost-diary [26]. We considered this too burdensome for the participants. Indirect health care costs (costs which are made during extra gained years of life) and indirect non health care costs (the value of production lost to society due to illness-related absence from work and days of inactivity) are often also included in an economic evaluation. We decided however not to include those costs, because of their limited relevance in a population of retired elderly people.

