**Methods/design:**

The study is carried out as a parallel group randomised trial. To screen eligible participants, we sent a postal questionnaire to 4901 elderly people (70–84 years) living at home in a town in the south of the Netherlands. After applying inclusion criteria (e.g., self-reported poor health status) and exclusion criteria (e.g., those who already receive home nursing care), we selected 330 participants. They entered the randomisation procedure; 160 were allocated to the intervention group and 170 to the control group. The intervention consists of (at least) 8 systematic home visits over an 18 months period. Experienced home nurses from the local home care organisation carry out the visits. The control group receives usual care. Effects on health status are measured by means of postal questionnaires after 12 months, 18 months (the end of the intervention period) and after 24 months (the end of 6-months follow-up), and face-to-face interviews after 18 months. Data on mortality and service use are continuously registered during 24 months. A cost-benefit analysis is included.

The design and setting of the study, the selection of eligible participants and the study interventions are described in this article. Other included items are: the primary and secondary outcome measures, the statistical analysis and the economic evaluation.

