This study will investigate the effects of systematic home visits by home nurses to elderly people with (perceived) health problems in terms of their health status, the use of care services and the cost-effectiveness. We expect that the visits will improve the functional abilities, perceived health and quality of life of the participants. We also hypothesize that they will reduce specialist care, institutionalisation, especially hospital (re-) admissions, and total health care expenditures. Evidence regarding the usefulness of the proposed risk group approach is needed to decide on the future implementation of the visits. This article presents the design of this new trial.

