## Methods/design

### Study design and setting

The study is carried out as a parallel group randomised trial. It is conducted in co-operation with a large home care organisation in the south of the Netherlands (Sittard and surroundings). The addresses we used to screen eligible persons for the study were drawn from the population register of the municipality. After the screening procedure we randomised 330 elderly. Effects of the intervention are measured by means of postal questionnaires after 12 months, 18 months (at the end of the intervention period) and after 24 months (at the end of a 6-months follow-up period) and by face-to-face interviews after 18 months. Mortality and data on the use of care services are continuously registered over the 24-months research period. A cost-benefit analysis is also included. The design of the study is shown in figure 1. The design is, unless otherwise mentioned, carried out according to plan.

The study has obtained the approval by the Medical Ethical Committee of Maastricht University/Academic Hospital Maastricht.

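### The economic evaluation is called societal but counts only direct health care costs, and it is named cost-benefit in two places and cost-effectiveness in two others

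*Protocol article*

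**What the plan says.** All references are to the protocol article.

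- **Perspective.** The Economic evaluation section opens: "A cost-effectiveness analysis will be carried out in which we consider costs from a societal perspective".
- **Costs kept.** It then sets the scope: "In this study we will include direct health care costs". These are explained as the costs of the visiting programme (screening, nurses' pay, travel and training, among others) and the costs of participants' health care.
- **First exclusion.** "Direct non health care costs (e.g., the travel costs made by participants) are not included". The reason is that such costs would best be collected with a cost diary: "We considered this too burdensome for the participants".
- **Second and third exclusions.** The section describes indirect health care costs (those arising in extra years of life) and indirect non-health-care costs (lost production and inactivity). It leaves out both for one reason: "We decided however not to include those costs, because of their limited relevance in a population of retired elderly people".
- **Name of the analysis.** The Methods/design part of the abstract says "A cost-benefit analysis is included", and Study design and setting says "A cost-benefit analysis is also included". The aim at the end of the Background lists "the use of care services and the cost-effectiveness", and the Economic evaluation section again uses cost-effectiveness.

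**The concern.** A societal perspective counts costs whoever bears them: the health service, the participant, the household or anyone else. An evaluation limited to programme and health care costs takes a health-care perspective. That is a legitimate choice, but it answers a narrower question.

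The type of analysis matters in the same way. A cost-benefit analysis puts a money value on outcomes. A cost-effectiveness analysis sets costs against outcomes in their own units. A reader of the abstract is told to expect the first, while the section that describes the method announces the second.

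What is at stake is what the economic result may be said to show. The Background says that the evidence is meant to inform a decision on implementing the visits. A result reported as societal would suggest that costs falling on participants and households had been weighed, when the plan leaves them out.

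**Working it through.** No arithmetic beyond counting applies, and the plan gives no figure to reproduce. The check sets the statements side by side.

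**Step 1: perspective against cost scope.** The Economic evaluation section supplies its own classification:

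| Cost class | Treatment | Reason given |
|---|---|---|
| Direct health care (programme plus participants' care) | included | – |
| Direct non-health-care | excluded | burden of a cost diary |
| Indirect health care | excluded | retired population |
| Indirect non-health-care | excluded | retired population |

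One class of four is kept and 4 − 1 = 3 are excluded. A few included items, such as meals on wheels, could be argued to lie outside strict health care, but the section itself lists them as health care costs. On the document's own terms the scope is health care and programme costs.

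**Step 2: do the reasons support the societal label?** There are two reasons, and they differ in kind.

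- The cost-diary reason is one of feasibility. It explains why direct non-health-care costs are not collected. It does not show that they are nil or irrelevant to society.
- The retirement reason is one of relevance, and it is applied to both indirect classes. It fits lost production, since retired people lose little paid work. It has no evident bearing on health care used in gained years of life, which does not depend on whether a person is employed. That exclusion therefore has no reason that fits it.

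**Step 3: name of the analysis.** Cost-benefit appears twice (abstract; Study design and setting). Cost-effectiveness appears twice (aim in the Background; Economic evaluation). The only valuation step described multiplies resource quantities by unit costs, which is a valuation of inputs. The measures in the Outcome measures section are health and service-use measures, and no money value is attached to them there. The described method thus fits the cost-effectiveness name.

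**Step 4: can a direction of bias be derived?** The omitted costs could run either way.

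- If fewer admissions meant more unpaid care by family, leaving that care out would favour the visits. No section says that care shifts in this way.
- The one omitted item that the section names is participants' travel. In the earlier trial's poor-health subgroup, outpatient referrals were 61% with visits against 79% without, and hospital admissions 47% against 74% (Background). If that pattern recurred, visited participants would travel less, and omitting their travel would count against the visits. The nurses' own travel is already charged to the programme.

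The document gives no amounts for either item, so neither the size nor the sign of the net effect follows.

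**The case against.** The strongest reply is that nothing is hidden. Each exclusion is stated, classified and explained in the same section as the word *societal*, so a careful reader of that section would not be misled. The hypothesis in the Background concerns total health care spending, which is what the plan counts. The listed items span several services and are wider than one payer's view. The article is also condensed: its cost lists are open-ended, and a fuller document might name the effect measure.

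Much of this stands. The fault is one of labelling, not concealment, and the lack of detail on unpaid care or on an effect measure is no finding in itself. But disclosing the exclusions does not make the declared perspective true, and the abstract carries neither the exclusions nor the name that the method section uses. A fuller document could add detail, but it would not reconcile two different names within this article.

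Two stronger readings are tempting and are not supported.

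- **That the omissions tilt the result toward the visits.** This needs a shift of care to families that the document does not describe, and omitted participant travel could work the other way.
- **That a fall in mortality would make the omitted costs of gained life-years large.** The earlier figures (24% against 40%) are three-year rates in a subgroup of 57 + 53 = 110 people, whereas service use here is registered over 24 months. Nothing in the section excludes survivors' health care costs within those 24 months.

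Nor is it right that one reason is stretched over every exclusion: the retirement argument covers only the two indirect classes.

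**Conclusion.** The point holds as a contradiction within the article. The evaluation is declared societal, but by its own classification it keeps one cost class of four. The analysis has two names that denote different methods, and the method described fits only one of them. The retirement argument also leaves the exclusion of health care costs in gained life-years without a fitting reason.

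The conclusion rests on the usual meanings of societal perspective and cost-benefit analysis, and on the article's own wording. It needs no assumption about effect sizes. The consequence is confined to what the economic result may claim. The net direction of any bias cannot be determined, and the health outcomes, the randomisation and the sample size are untouched. The correction should be made before the economic results are reported, but it is not a threat to the trial.

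**What to change.** 1. Use one name in the abstract, the design section, the Economic evaluation section and the report: a cost-effectiveness analysis from a health-care perspective. Drop *societal* and *cost-benefit*.
2. Limit the economic conclusion to programme and health care costs within the 24-month registration period, and say that no claim is made about costs to participants, households or society at large.
3. Keep the cost-diary reason for direct non-health-care costs, and confine the retirement argument to production losses.
4. Give a separate reason for leaving out health care costs in gained life-years; the 24-month horizon could serve.

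The change is to wording and needs no new data. The downside is a narrower economic claim.
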